### Procedure for unblinding if needed {17b}

During the trial, if the intervention group participants occur any emergent situation such as vaginal bleeding, fetal heartbeat complication etc., we will inform them and allow them to decide whether continue to participate in the study.

## Data collection and management

### Plans for assessment and collection of outcomes {18a}

The principal researcher and an assistant researcher will perform data collection. Prior to the study commencing, the research team conducted an online discussion to clarify the research protocol (Fig. 4).

**Fig. 4 Fig4:**
[figure not shown]
Study protocol

### Primary outcome measures

#### Decisional Conflict

The DCS was originally developed by O’Connor of the University of Ottawa [40] and was revised for this specific decision by Shorten [41]. It consists of 18 questions in five subscales measuring; certainty, informed, values, supported, and quality. A 5-point Likert-type scoring method is adopted, with each item scored from 1 to 5 points indicating strongly agree to strongly disagree, respectively. An average score <2.0 indicates readiness for decision-making. Higher scores indicate higher degrees of decision conflict. In Japan, Cronbach’s α of DCS is 0.86 [42].

### Knowledge

Knowledge measurement consists of a 15-item questionnaire which presents a series of statements regarding risks and benefits of each birth mode [41]; answering ‘true,’ ‘false,’ or ‘unsure’. Negative scoring is applied, awarding a score of + 1 for a correct answer’, -1 for an incorrect answer and zero for an “unsure” response. Previously tested Cronbach *α* for this questionnaire was = 0.67 [41].

### Birth mode preference

Women’s birth mode preference is assessed on a 15-point scale with anchor points for VBAC and ERCD. Birth preference will be measured and recorded using the 15-point scale as a rating of strength of women’s birth method preference [41].

### Decision-aid acceptability

Decision-aid acceptability includes nine questions to measure women’s rating of the birth decision-aid platform using a 5-point Likert scale ranging from ‘not at all’ (1 point) to ‘a great deal’ (5 points) [37].

### Secondary outcome measures

#### Actual birth outcome

The principal researcher will ask women about their actual birth outcome one month after birth via Line App and verify this with the medical record.

### Satisfaction with decision scale (SWD)

SWD is assessed using six questions to measure women’s satisfaction with their decision. The 5-point Likert scale ranges from “strongly agree” (5 points) to “strongly disagree” (1 point). Women have higher scores indicating increased satisfaction. SWD [43]. Cronbach’s α previously tested was 0.88 [44].

### Plans to promote participant retention and complete follow-up {18b}

Reminders will be sent to participants through the Line app to complete questionnaire at three scheduled times (14–16-weeks’ gestation and 35–38 weeks’ gestation and one month after birth). Eligible participants will receive up to $300 Taiwanese (NTD) compensation for participating one month after birth. The research team will have weekly meetings to monitor the adherence and retention of participants.

### Data management {19}

The encrypted data will be stored securely for six years in the principal researcher’s password protected computer in a locked office. Data will be maintained in a secure database that only the study investigators will have access to the final trial dataset and disclosure of contractual agreements.

### Confidentiality {27}

As per institutional approval, the data will be encrypted. Each participant will be identified by alphabetical codes (A, B, C, etc.).

### Plans for collection, laboratory evaluation and storage of biological specimens for genetic or molecular analysis in this trial/future use {33}

There will be no biological specimens collected.

## Statistical methods

### Statistical methods for primary and secondary outcomes {20a}

Analysis will be by intention to treat. Data will be processed and analyzed using IBM SPSS version 28.0 software. Descriptive statistical analysis will include frequency, percentage, mean and standard deviation for each variable; chi-square test and Student’s t-test will be used to compare the differences between groups for the homogeneity of basic attributes. Statistical significance will be established using an α of 0.05. Bivariate analyses and linear regression models will be used to examine determinants of primary outcomes (decisional conflict score, knowledge score, birth mode preference), and secondary outcomes (mode of birth and satisfaction with decision). The strength of women’s birth mode preference will be analyzed using a non-parametric test (Wilcoxon signed-rank test).

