### Sample size {14}

Sample size was calculated using G-POWER 3.1.9.2 software. Based on estimates from a previous pilot study [39], effect size = 0.50, a total of sample size 128 provided α = 0.05 and power = 0.80. To allow for preterm deliveries, mal-presentations, and losses to follow-up, an increase in the desired number by 20 percent would be 154.

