## Assignment of interventions: allocation

### Sequence generation {16a}

Using computer permuted block randomization.

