### Implementation {16c}

The principal research [name] will generate the allocation sequence, enrol participants, and assign participants to either control group or intervention group.

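### Significance tests of baseline homogeneity between randomised arms can mislead; describe baseline without p-values and adjust for pre-named baseline scores whatever the balance

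*Protocol article*

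**What the plan says.** In the protocol article, section {20a} on statistical methods plans frequencies, percentages, means and standard deviations for each variable, and adds that "chi-square test and Student’s t-test will be used to compare the differences between groups for the homogeneity of basic attributes". The next sentence reads "Statistical significance will be established using an α of 0.05". It does not name the homogeneity tests, but no other level appears anywhere.

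The groups compared are randomised: "Using computer permuted block randomization" (section {16a}). Their size comes from section {14}: "effect size = 0.50, a total of sample size 128", at a two-sided 0.05 level by inference and power 0.80, then "an increase in the desired number by 20 percent would be 154".

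For the outcomes, section {20a} says "Bivariate analyses and linear regression models will be used to examine determinants of primary outcomes", and extends this to the secondary outcomes. It does not say which variables enter those models and does not link them to the baseline tests. It also does not say what follows from a significant or a non-significant homogeneity test.

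The outcomes and timeline sections ({12}, {13}) show that decisional conflict, knowledge and birth mode preference are measured in all women at 14–16 weeks and again at 35–38 weeks.

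**The concern.** A significance test asks whether two groups could have come from the same population. After proper randomisation that is already known to be so, and a small p-value then only marks a chance event. What a reader wants to know is different: whether the observed imbalance is large enough, in a variable that matters enough, to distort the arm comparison. The p-value does not answer that. It depends on the sample size and takes no account of how strongly the attribute predicts the outcome.

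Two things are at stake. The first is the statement on comparability in the trial report, which can reassure or alarm for the wrong reason. The second is precision. Baseline scores of three primary outcomes are collected in everyone, yet the only between-arm use of baseline attributes that the article states is the homogeneity test.

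**Working it through.** **Inputs.** From section {14}: effect size 0.50, total 128, α = 0.05, power 0.80, raised to 154. From section {20a}: t-test and chi-square test, 0.05. Assumed, because not stated: 1:1 allocation (64 per arm analysed, or 77 per arm recruited), two-sided tests, the number of baseline attributes (5 to 20), and the correlation r between a baseline score and its outcome (0.4 to 0.6).

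**1. The plan's own figure.** Two-sample t-test, noncentrality d·√(n/2) = 0.50 × √32 = 2.83, 126 degrees of freedom, critical value 1.979. Power is 0.801, so 64 per arm, 128 in total, reproduces the stated size. 128 × 1.2 = 153.6, rounded to 154, or 77 per arm.

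**2. What passes as homogeneous.** The largest observed standardised difference that stays non-significant is t(0.975) × √(2/n).
- 64 per arm: 1.979 × 0.1768 = 0.350 SD.
- 77 per arm: 1.976 × 0.1612 = 0.318 SD.

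For an attribute present in about half the women, the limit is 1.96 × √(0.25 × 2/n): 17 percentage points at 64 per arm and 16 at 77.

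**3. What is flagged.** Under proper randomisation each test is significant with probability about 0.05. For k independent attributes the chance of at least one flag is 1 − 0.95^k:

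| k | 5 | 10 | 15 | 20 |
|---|---|---|---|---|
| at least one chance flag | 23% | 40% | 54% | 64% |

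**4. What a passing imbalance could do to an unadjusted comparison.** The shift in the arm difference is r × imbalance. At the 64-per-arm limit of 0.350 SD it is 0.14, 0.175 and 0.21 SD for r = 0.4, 0.5 and 0.6, which is 28%, 35% and 42% of the 0.50 effect. This is an edge case. For any one attribute, the chance of an observed imbalance of at least 0.3 SD that still passes is P(\|t\| ≥ 0.3/√(2/n)) − 0.05:
- 64 per arm: 0.092 − 0.05 = 0.042.
- 77 per arm: 0.065 − 0.05 = 0.015.

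**5. What adjustment would give.** Including a baseline score correlated r with the outcome reduces the residual SD by √(1 − r²). The effective standardised effect becomes 0.50/√(1 − r²), with 125 degrees of freedom and 64 per arm:

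| r | effective d | power |
|---|---|---|
| none included | 0.500 | 0.80 |
| 0.4 | 0.546 | 0.865 |
| 0.5 | 0.577 | 0.90 |
| 0.6 | 0.625 | 0.94 |

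**The case against.** The strongest reply is that the plan attaches no decision to these tests. It does not say that the arms will be called homogeneous when p exceeds 0.05, nor that covariates will be chosen from the results. This stands, and it rules out three stronger readings that a reader might infer.

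- *The comparability statement will be wrong.* This does not follow. Most attributes may well be balanced, and the same section plans the descriptive figures in which an imbalance would be visible. The tests can mislead; they need not.
- *The error rate of the arm comparison is inflated.* Averaged over randomisation the unadjusted test keeps its 5%. It is tempting to look only at trials whose baseline difference has \|z\| between 1 and 1.96, where the rate is about 6.6%, 7.4% and 8.2% for r = 0.4, 0.5 and 0.6 (normal approximation). That is a selected band of about 27% of trials. Where \|z\| is below 1, the rate is 3.7%, 3.1% and 2.3%. Over all trials that pass the test it is 4.6%, 4.3% and 4.0%, below nominal.
- *Adjusting only after a significant baseline test loses power.* That would be so, but the document contains no such rule, so it cannot be held against the plan.

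Two further replies have some weight. Naming covariates is commonly left to a statistical analysis plan, and none is shown. Its absence here is not the finding; the point rests on the tests that the article does state. If the analysis plan already includes the baseline scores, the precision gain is already secured. Also, one person "will generate the allocation sequence, enrol participants, and assign participants to either control group or intervention group" (section {16c}), so a baseline difference in this trial need not be chance alone, and a test could hint at faulty allocation. Even then a p-value does not measure how much the difference matters for the outcome, and a non-significant one does not rule the problem out.

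**Conclusion.** The point holds in a limited form. The planned homogeneity tests are uninformative about what they are meant to show: they pass observed differences up to 0.32–0.35 SD, and under proper randomisation what they flag is chance. No stated inference about the intervention depends on them, so the harm is confined to how comparability is reported and to precision that may go unused.

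The larger practical gain comes from the baseline scores: power of about 0.865 to 0.94 instead of 0.80 at d = 0.50 with 64 per arm. It rests on assumed correlations of 0.4 to 0.6, which the documents do not give, on 1:1 allocation, and on reading the 0.50 as the standardised difference in the outcome without baseline adjustment. A weaker correlation gives a smaller gain.

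**What to change.** In section {20a}:

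1. Remove the chi-square and t-tests of baseline homogeneity. Present basic attributes by arm as counts and percentages or means and standard deviations, with standardised differences and no p-values.
2. State that the arm difference in each continuous outcome is estimated with a linear model containing treatment arm and prognostic variables from the 14–16 week survey, named in advance. For decisional conflict, knowledge and birth mode preference at 35–38 weeks, include the baseline value of the same measure.
3. State that these variables are included whatever the observed balance.

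This is a few sentences, with no new data, no extra women and fewer tests. The one cost is that the covariates must be fixed before the data are seen.

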### Trial design {8}

The Ottawa Decision Support Framework (ODSF) is utilized in the trial design [32]. Figure 1 outlines the larger multi-phase mixed methods study design sequence which the current study is nested into [17, 29, 30, 34]. The current study represents Aim 4 (Intervention implementing phase) (Fig. 1) and is a randomized control trial design. Stage 1 involves a randomized pre-test and post-test experimental design; decisional conflict, knowledge, birth mode preference, and decision-aid acceptability will be assessed. Stage 2 comprises a survey to measure actual birth outcome (VBAC or ERCD) and satisfaction.

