### Outcomes {12}

Primary outcome measures include decisional conflict (time frame: 14–16-weeks’ gestation and 35–38 weeks’ gestation), knowledge (time frame: 14–16-weeks’ gestation and 35–38 weeks’ gestation), birth mode preference (time frame: 14–16-weeks’ gestation and 35–38 weeks’ gestation), and decision-aid acceptability (time frame: 35–38-weeks’ gestation).Secondary outcome measures include actual birth outcome (time frame: one month after birth) and satisfaction with decision scale (SWD) (time frame: one month after birth).

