### Concealment mechanism {16b}

A parallel group of participants will be allocated to either control group (usual care) or intervention group (usual care plus the birth decision-aid platform) in a quiet examination room in accordance with sequentially numbered computer permuted block randomization.

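### The test named for the primary outcome birth mode preference, Wilcoxon signed-rank, measures change within women and does not compare the randomised arms

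*Protocol article*

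**What the plan says.** Section {8} describes the design: "Stage 1 involves a randomized pre-test and post-test experimental design". Section {12} lists among the primary outcomes "birth mode preference (time frame: 14–16-weeks’ gestation and 35–38 weeks’ gestation), and decision-aid acceptability". The measure itself is defined under its own heading: "Women’s birth mode preference is assessed on a 15-point scale with anchor points for VBAC and ERCD". Section {16b} describes parallel allocation to usual care or usual care plus the platform, and nothing in the article describes matching of women across arms.

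Section {20a} makes three statements that bear on the comparison of arms.

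- Chi-square and t-tests will "compare the differences between groups for the homogeneity of basic attributes".
- "Bivariate analyses and linear regression models will be used to examine determinants of primary outcomes", with decisional conflict, knowledge and birth mode preference named as those outcomes. Neither arm nor the baseline score is named as a term.
- The strength of "birth mode preference will be analyzed using a non-parametric test (Wilcoxon signed-rank test").

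The only outcome for which a control-versus-intervention comparison is spelled out is decision-aid acceptability, in section {20b}.

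**The concern.** The signed-rank test works on paired differences. With unmatched arms, the only pairs are a woman's two scores. Its null hypothesis is no change over time, and arm membership does not enter the calculation.

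Movement under usual care is plausible from the protocol itself. About 20 weeks separate the two surveys, and section {13} has all participants confirm their preferred birth mode with the obstetrician before the later one. A significant signed-rank result would therefore be compatible with no effect of the decision aid.

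The same outcome also appears under the regression models. So two analyses that answer different questions are named for one primary outcome, with no order between them. The more specific of the two is the one that does not use the randomisation.

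**Working it through.** **1. What the sample size was built for.** Section {14} gives effect size 0.50, α 0.05, power 0.80 and a total of 128. Assume a two-sided test and equal allocation, since neither is stated.

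- Two-sample t-test: the noncentral-t calculation gives 63.8, so 64 per arm, 128 in total, with power 0.801. This reproduces the stated figure.
- Paired t-test at d = 0.50: 33.4, so 34 women in total. This does not reproduce it.

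The trial is thus sized for a contrast between arms, while the test named for this outcome is a paired one.

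**2. How the signed-rank test behaves when both arms drift equally and the arm effect is zero.**

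Inputs from the protocol: a 15-point scale, and 154 women less 20% loss (154 × 0.80 = 123.2, about 62 per arm).

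Assumed inputs, not in the protocol: SD 3.5 points at each time, pre-post correlation ρ = 0.5, and a common drift of 0.5 or 1 point.

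SD of the change = 3.5 × √(2(1 − 0.5)) = 3.5. The expected statistic is roughly z = √0.955 × drift / (3.5/√n), where 0.955 is the efficiency of the signed-rank test relative to the t-test under normality. The chance of p < 0.05 is about Φ(z − 1.96).

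- Intervention arm, n = 62, 0.5 point: z = 0.977 × 1.125 = 1.10, chance about 0.20.
- Intervention arm, n = 62, 1 point: z = 0.977 × 2.250 = 2.20, chance about 0.59.
- Both arms pooled, n = 124, 0.5 point: z = 0.977 × 1.591 = 1.55, chance about 0.34.
- Both arms pooled, n = 124, 1 point: z = 0.977 × 3.182 = 3.11, chance about 0.87.

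Simulation on the rounded, bounded 15-point scale agrees:

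| Common drift, no arm effect | Signed-rank, intervention arm | Signed-rank, pooled | Rank-sum on change, between arms |
|---|---|---|---|
| 0.5 point | about 19% | about 32% | about 5% |
| 1 point | 58–62% | 87–91% | about 5% |

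The size depends on the assumed drift. The direction does not: any common drift raises the signed-rank rate and leaves the between-arm test near its nominal level.

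**3. What a baseline-adjusted comparison would give at the planned size.** With 64 per arm and d = 0.50, the expected statistic is √(64/2) × 0.50/√(1 − ρ²) = 5.657 × 0.50/√(1 − ρ²), and power is about Φ(that − 1.96). The correlations are assumed.

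- ρ = 0.3: 5.657 × 0.524 = 2.96, power about 0.84.
- ρ = 0.5: 5.657 × 0.577 = 3.27, power about 0.90.
- ρ = 0.6: 5.657 × 0.625 = 3.54, power about 0.94.

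The unadjusted comparison has 0.80. The planned number is therefore enough for a baseline-adjusted comparison of the arms at this effect size.

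**The case against.** Four points on the other side deserve weight.

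- **Signed-rank is not the only analysis named for preference.** The regression sentence also covers it, and nothing there excludes arm and baseline score as terms. This stands, and it rules out saying that the plan contains no possible comparison of the arms. It does not repair the signed-rank sentence, because no precedence is given and arm is not identified as the effect of interest.
- **Covariate lists are commonly left to the full protocol or analysis plan.** This also stands. A reader might infer that no baseline-adjusted arm effect is planned for any primary outcome. The article does not support that: the models are unspecified, not specified wrongly. Decision-aid acceptability has no baseline to adjust for, and its arm comparison is stated in section {20b}. A later document could fill in regression terms, but it would have to reverse the signed-rank sentence.
- **In a pre-test and post-test design, a test of within-woman change is a legitimate description.** It is, but section {20a} does not label it as description. It stands under the methods for primary and secondary outcomes.
- **The harm is inferred.** A reader might conclude that a shift common to both arms will be reported as the effect of the decision aid, or that the arms will be judged by significance in one and not the other. No sentence says either. The percentages above are the test's power to detect a real change over time. They become false claims about the decision aid only if the result is read that way.

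**Conclusion.** The point holds for the signed-rank sentence. As written, the test named specifically for one of four primary outcomes cannot show whether the decision aid moved preference more than usual care did. This follows from the design and needs no assumed figures. The illustrative sizes (about 19% and about 60% in the intervention arm, against 5% for a between-arm test) rest on an assumed SD of 3.5, a correlation of 0.5 and drifts of 0.5 and 1 point, none of which the protocol gives.

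The double listing under regression is an ambiguity to resolve, not evidence that the arms will go uncompared. Baseline adjustment for decisional conflict and knowledge is an improvement in precision and not the correction of an error, since an unadjusted randomised comparison is valid.

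**What to change.** Replace the signed-rank sentence in section {20a}. Suggested content:

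- The primary analysis of birth mode preference compares the arms on the 35–38-week score, in a linear or proportional-odds model with randomised arm and the 14–16-week score as terms. It reports the adjusted arm effect with a 95% confidence interval.
- A rank-sum test of the arms on change in score is the non-parametric check.
- Signed-rank tests, if kept, describe change within each arm and are not used to compare arms.
- Regressions for determinants are labelled exploratory.

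As an improvement at no cost, use the same arm-plus-baseline model for decisional conflict and knowledge, whose baseline scores are already scheduled. Leave decision-aid acceptability out of this, as it is measured once.

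The cost is a few lines of text. No added women, visits or questionnaires are needed. The change should be made and dated before outcome data are analysed by arm.

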### Interim analyses {21b}

No interim analyses are planned.

### Methods for additional analyses (e.g. subgroup analyses) {20b}

Analysis of decision aid acceptability subgroup will be conducted to assess the differences between control and intervention group.

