### Interventions

#### Explanation for the choice of comparators {6b}

The control group condition is essentially ‘usual care’ and will enable comparison with the experimental condition in regard to the shared decision making intervention only, thereby minimizing the potential impact of any additional variables in the experiment. A maternal health booklet, produced by Health Promotion Administration, Ministry of Health and Welfare, Executive Yuan, Taiwan, will be provided to all women in the study [35]. The 58-page booklet is routinely provided to all women during pregnancy in Taiwan and includes Five (5) “Dos” and “Do nots” during pregnancy. Five (5) “Dos” content includes (1) Do receive prenatal exams according to schedule; (2) Do take good care during pregnancy; (3) Do recognize pregnancy complications; (4) Do know the signs of premature birth; (5) Do know the signs of labor. Five (5) “Do nots” content includes (1) Do not smoke or drink; (2) Do not be exposed to secondhand smoke; (3) Do not take medication without doctor’s orders; (4) Do not choose a C-section to pick the time of birth; (5) Do not use drugs [35]. There is very limited information relevant to mode of birth choice after caesarean.

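### Decision-aid acceptability cannot be compared between arms as planned, because control women never receive the platform that the items rate

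*Protocol article*

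**What the plan says.** All references are to the Protocol article.

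- **Status.** Outcomes {12} opens its list with "Primary outcome measures include decisional conflict", continues with knowledge and birth mode preference, and closes it with "and decision-aid acceptability (time frame: 35–38-weeks’ gestation". Acceptability is thus one of four primary outcomes, measured once, with no baseline.
- **What is rated.** The section Decision-aid acceptability states: "Decision-aid acceptability includes nine questions to measure women’s rating of the birth decision-aid platform". Each item is scored from 1 to 5.
- **Who has the platform.** Concealment mechanism {16b} has women "allocated to either control group (usual care) or intervention group (usual care plus the birth decision-aid platform". Intervention description {11a} and Participant timeline {13} agree: access and log-in details are described for the intervention group only.
- **What controls have.** Explanation for the choice of comparators {6b} says: "The control group condition is essentially ‘usual care". The general maternal booklet goes to every woman in the study, and of it the section says: "There is very limited information relevant to mode of birth choice after caesarean".
- **Planned analysis.** Methods for additional analyses {20b} consists of one sentence: "Analysis of decision aid acceptability subgroup will be conducted to assess the differences between control and intervention group".
- **Main analysis.** Statistical methods {20a} names three primary outcomes for its bivariate analyses and regression models: decisional conflict, knowledge and birth mode preference. Acceptability is not among them.

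**The concern.** A randomised comparison needs an outcome that can be observed with the same meaning in both arms. Here the outcome is an opinion of the intervention itself, and one arm does not have the intervention. The difference described in {20b} therefore estimates nothing of interest.

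There are two ways it could play out. If controls leave the items blank or are never shown them, the complete-case rule in {20c} leaves no control data. If controls do answer, they score a product they have not used, and the contrast separates women who had a log-in from women who did not. Either result would be attached to an outcome declared primary in a randomised trial, where a reader would expect evidence of effect.

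The disagreement between {12} and {20a} adds to this. An outcome is called primary in one section, is left out of the primary list in another, and has its only specific analysis in a third, under additional analyses, where it is called a subgroup.

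**Working it through.** **1. The sections side by side**

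| Question | Section | Answer |
|---|---|---|
| Is acceptability primary? | Outcomes {12} | Yes, one of four |
| Is it in the primary list of the main analysis? | Statistical methods {20a} | No, three are named |
| What is rated? | Decision-aid acceptability | The platform |
| Who has the platform? | {11a}, {13}, {16b} | Intervention arm only |
| What do controls have? | {6b} | Usual care and the general booklet |
| Who completes the items? | Participant timeline {13} | Not limited to one arm in the text |
| What comparison is planned? | {20b} | Control against intervention |

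No section gives controls access to the platform before 35–38 weeks, and none gives them another object to rate. The number of controls able to rate the platform is therefore 0 of about 64 (128/2, assuming 1:1 allocation, which the article does not state). The contrast cannot be estimated at any sample size.

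**2. The plan's own figure**

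Sample size {14} gives effect size 0.50, α = 0.05, power 0.80, total 128, then 154 after a 20 percent increase. For a two-sample t-test, assuming a two-sided test and 1:1 allocation:

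- Normal approximation: n per arm = 2 × (1.96 + 0.84)² / 0.50² = 62.7, rounded up to 63, total 126.
- Exact t calculation: 63.77 per arm, rounded up to 64, total 128. This matches.
- Increase: 128 × 1.20 = 153.6, rounded up to 154. This matches.

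Nothing in that section ties the calculation to acceptability, and removing the comparison in {20b} changes neither figure.

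**3. What one arm can deliver**

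Half-width of a 95% CI with n intervention raters:

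- mean rating, in SD units: 1.96/√n
- proportion, at its widest (p = 0.5): 1.96 × √(0.25/n)

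| n | Basis (1:1 assumed) | Mean | Proportion |
|---|---|---|---|
| 62 | 77 recruited per arm (154/2), 20% lost: 77 × 0.8 = 61.6 | 0.249 SD | 0.124 |
| 64 | the plan's completers, 128/2 | 0.245 SD | 0.1225 |
| 77 | no loss | 0.223 SD | 0.112 |

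Using the t quantile for 62 raters in place of 1.96 gives 0.254 SD. A descriptive one-arm estimate is therefore feasible with the planned numbers.

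**The case against.** The strongest case on the other side is that little depends on this sentence. It stands under additional analyses, the main analysis does not model acceptability, the sample size is not tied to it, and {20a} already promises frequencies, means and standard deviations for every variable. All of that stands, and it limits the harm. It does not make the stated comparison valid, and the descriptive promise in {20a} does not cancel the comparison in {20b}.

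A second argument is that the wording is loose and might mean subgroups defined by level of acceptability. That reading fails as well, because controls would have no rating by which to be classified. Nor can controls be taken to rate the booklet, since the instrument is defined by "rating of the birth decision-aid platform using a 5-point Likert scale". The schedule and flow figures are not available here and may restrict the items to one arm; if so, {20b} would still contradict them.

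A reader might infer several stronger things that the documents do not support:

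- **That the comparison would produce a spurious significant result favouring the intervention, because non-users would choose the lowest score.** The nine items are not reproduced, and controls may never be asked, so neither the direction nor the existence of such a result is established.
- **That controls are certain to be given the items.** The text only fails to exclude it.
- **That the trial's evidence on effectiveness is undermined.** The other three primary outcomes do not depend on this comparison.
- **That acceptability must come off the primary list.** Once no between-arm test is made, it could stay there as a one-arm descriptive outcome. Recruitment began in September 2021, so changing its designation is not merely a matter of wording.

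**Conclusion.** The comparison of acceptability between arms is wrong as written. The outcome is a rating of the platform, only one arm receives the platform, and {20b} nonetheless commits to a control-versus-intervention difference. This is a contradiction between stated passages, not a detail left to an analysis plan. A plan that followed {20b} would inherit the error.

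Its size is best stated structurally: one of four declared primary outcomes has no valid control value. The effect is confined to that outcome. The conclusion rests only on the text; the 1:1 ratio and the completer numbers are assumptions needed solely for the precision figures. The inconsistency over whether acceptability is primary is a separate, smaller fault that the same revision should settle.

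**What to change.** Make three linked changes.

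1. In {20b}, delete the between-arm comparison. State that acceptability will be reported descriptively in the intervention arm only, as a mean or proportion with a 95% CI.
2. In Participant timeline {13}, state that only intervention women complete the nine items at 35–38 weeks, and check that the schedule and flow figures agree.
3. Align {12} and {20a} so that acceptability is not presented as a between-group primary efficacy outcome. Either list it explicitly as a one-arm descriptive outcome or move it off the primary list. Document and date the change, since recruitment has started.

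The cost is an amendment to outcome and analysis wording, plus a matching check of any registered outcome list. If controls are at present given the items, their survey becomes nine items shorter. Sample size, randomisation and the analyses of decisional conflict, knowledge and birth mode preference stay as they are.
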